### C) Economic Evaluation

Resource use for the PFMT will be collected. Resource use will be recorded prospectively for every woman within the study. For the PFMT intervention, cost details will be gathered from the Intervention Therapists, recorded at the time of intervention (e.g. length of appointments, materials used). Data on the use of primary and secondary care services by the women, including medications, GP visits and uptake of surgery, will be collected using participant questionnaires devised by the research team which will be administered at each of the follow up time periods. Unit costs/prices for resource use will be obtained using published estimates for health care services and/or interventions. Costs to the women will be collected in the participant questionnaires. Data will be collected on the mode of travel, cost of travel if applicable, amount of time the women take out of their usual activities such as work, to go to the appointments and similar data from family members that either accompany them or look after their children.

To measure health outcomes, the EQ-5D-5 L generic instrument will be used [22]. This instrument will provide the quality of life weights (utility values) to compute quality adjusted life years (QALYs). Study participants will complete the EQ-5D-5 L generic instrument within the questionnaires at baseline and at 6, and 12 months after randomisation.

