### B) Outcomes study

It is anticipated that each staff member in the five sites will recruit five women to take part in the study and who will: agree to complete study outcome questionnaires, have the POP-Q assessment (pre- and 6 months post) and take part in qualitative interviews if requested. Patient outcomes as used in the POPPY trial will be collected at baseline (immediately prior to first (assessment) appointment) and at six months and one year follow-up; clinicians will collect POP-Q data at baseline and 6 months during specified appointments and the remaining measures (POP-SS, EQ-5D-5 L, ICIQ-UI SF and patient demographic data all collated within patient completed questionnaire) will be collected by post at each time point.

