### B) Outcomes data

Descriptive statistics will be tabulated for all outcomes at each time point, showing means and SDs for POP − SS and EQ − 5D-5 L, proportions for POP − Q, the need for further treatment, and frequencies for the number of NHS contacts. Differences (and correlations where appropriate) between baseline and 6 − months and between baseline and 12 − months will be calculated. We will initially examine the differences before and after intervention using paired t-tests and chi-square tests. We will fit appropriate generalised linear models on the difference between outcomes before and after intervention, adjusting for baseline measurements and potential confounders (e.g. demographic factors, study site). If possible, we will also explore the effect of different levels of adherence to PFMT using structural mean models [28]. Complete case analyses will be performed throughout, with missing data being addressed in secondary analyses using multiple imputation methods.

POP − SS and EQ − 5D 5L will be treated as continuous data, POP − Q as ordinal, NHS contacts as count data and the need for further treatment (e.g. surgery or pessary) as binary data. In order to facilitate the understanding of prolapse related outcomes, individual items of the POP − SS will also be analysed separately and an additional dichotomous POP − Q measure (above/below the hymen) will be included in the analysis.

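### The planned change in NHS contacts, and the cost comparison between delivery models, have no stated baseline measure of service use

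*Protocol article*

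**What the plan says.** **Analysis.** In the protocol article, under Data analysis, B) Outcomes data: "Descriptive statistics will be tabulated for all outcomes at each time point". The number of NHS contacts and POP-Q are both named there. Differences from baseline to 6 months and from baseline to 12 months follow, with no outcome exempted. Models are then fitted to the before-after difference, "adjusting for baseline measurements and potential confounders". NHS contacts are to be handled as counts. Under C) Economic evaluation in the same part, costs and effects of the modes of delivery are compared, where appropriate with models of a similar kind.

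**Collection of service use.** Under Data collection, C) Economic Evaluation: "Data on the use of primary and secondary care services by the women, including medications, GP visits and uptake of surgery" come from participant questionnaires "which will be administered at each of the follow up time periods". Under B) Outcomes study, baseline is named separately, and the later collections are "at six months and one year follow-up". The measures posted at each time point are POP-SS, EQ-5D-5L, ICIQ-UI SF and "patient demographic data all collated within patient completed questionnaire".

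**Collection of POP-Q.** The same section says "clinicians will collect POP-Q data at baseline and 6 months during specified appointments", and earlier gives the same two-point schedule as a condition of taking part.

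**Outcome measures.** The booklet is said also to cover service-related outcomes, with need for further treatment as the example. A separate sentence lists extra content for the 6- and 12-month questionnaires.

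**The concern.** A change from baseline needs a baseline value, and the stated schedule appears to give none for service use. The consequence goes beyond one descriptive table. The Background says that the format of delivery is decided locally, so women are not randomised to a delivery model. If women seen under one model already used more services before treatment, that model may look more costly for reasons unrelated to PFMT delivery. Earlier service use is the most direct covariate for this, and it is best recorded before treatment starts.

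The POP-Q mismatch is smaller: the analysis text, read literally, asks for a 12-month tabulation and change that the schedule does not supply.

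**Working it through.** The document gives no figure on this point, so the check sets the planned analyses against the collection schedule.

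**Step 1: times at which each outcome is collected.** These come from Data collection B) and C) and from Outcome measures.

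| Outcome named in the analysis | Baseline | 6 months | 12 months |
|---|---|---|---|
| POP-SS | yes | yes | yes |
| EQ-5D-5L | yes | yes | yes |
| POP-Q | yes | yes | not scheduled |
| NHS contacts | not stated | yes | yes |

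**Step 2: planned differences that can be formed.** Each outcome has two planned differences, so these four have 4 × 2 = 8.

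- POP-SS: 2 of 2.
- EQ-5D-5L: 2 of 2.
- POP-Q: 1 of 2 (baseline to 6 months only).
- NHS contacts: 0 of 2.

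Three of the eight cannot be formed as described, and two of those three are NHS contacts.

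**Step 3: could follow-up include baseline for service use?** Two features of the text point the other way. Data collection B) separates baseline from follow-up. Data collection C) itself lists baseline alongside 6 and 12 months when it schedules the EQ-5D-5L, but not when it schedules service use.

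**Step 4: what remains for adjustment in the cost models.** Baseline POP-SS, EQ-5D-5L, ICIQ-UI SF and demographics are collected, and study site is named as a possible confounder. These help, but none measures earlier service use. Site adjustment has a further limit: where a delivery model is particular to one site, adjusting for site removes the contrast of interest.

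**Step 5: size.** Suppose follow-up use depends on earlier use with slope b, and two models differ by d in mean earlier use after the available adjustment. The contrast between models is then off by b × d. The document gives neither b nor d, so the bias cannot be quantified.

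For precision only, a linear adjustment for a baseline with correlation r removes a share r² of the variance. With r assumed to be 0.3 to 0.5, this is 0.3² = 9% to 0.5² = 25%. The correlations are assumptions, and counts and skewed costs need not follow the linear result, so the range is illustrative.

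**The case against.** The best counter-argument is the Outcome measures section. It places service-related outcomes in the booklet that also carries POP-SS at baseline, 6 and 12 months, and then lists follow-up additions separately. A baseline service-use item could therefore exist. In addition, the list of posted measures in Data collection B) is not exhaustive: it also omits adherence, women's own costs and need for further treatment. A journal article normally leaves booklet content to the full protocol.

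This leaves real doubt, but it does not settle the matter. The section does not name contacts, and its one example, need for further treatment, looks forward from the intervention. The only explicit schedule for service use is the follow-up one. If a baseline item does exist, that schedule still needs correcting.

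It can also be said that the sentence on differences is generic, that NHS contacts can be modelled as follow-up counts, and that the cost models are only to be similar where appropriate. That is fair, and it supports the fallback below. The text nevertheless exempts no outcome from the change analysis.

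Three stronger readings are tempting and should not be drawn:

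- **That nothing in the data could correct the cost comparison.** Other baseline covariates are available, so partial adjustment is possible.
- **That the sites are shown to differ in case mix.** Tables 1 and 2 describe location, POPPY experience and current service model. They report no patient characteristics, so imbalance in earlier service use is a possibility and not a documented fact.
- **That a 12-month POP-Q would be imputed for every woman.** Multiple imputation is planned for missing data, and an assessment that was never scheduled is not ordinarily counted as missing. The two-point schedule is clear, and analysts would probably follow it.

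**Conclusion.** The point holds on the plain reading. For all 120 women, neither planned NHS-contact difference can be formed from the stated schedule, and the cost comparison between non-randomised delivery models lacks a pre-treatment measure of service use. This rests on two assumptions: that follow-up means 6 and 12 months, as the article uses it elsewhere, and that the service-related outcomes in the booklet do not include contacts at baseline. The direction and size of any bias are unknown.

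The POP-Q mismatch is certain but minor and needs only a change of wording. The primary outcome, POP-SS, is measured at all three times and is unaffected. The case for acting is that the improvement is cheap, not that the cost results are shown to be wrong.

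**What to change.** 1. Add the primary care, secondary care and medication items of the follow-up questionnaires to the baseline booklet, with a stated look-back period. A window of the same length as the follow-up one makes the counts comparable. If the booklet already holds such items, correct the schedule in Data collection C) to say so.
2. Name this baseline service use as a covariate in the NHS-contact and cost models.
3. If baseline collection is no longer possible, drop the NHS-contact change analysis, analyse follow-up counts adjusted for the available baseline covariates, and state the limitation for the cost comparison.
4. In Data analysis B), limit POP-Q tabulation and change, including the above/below hymen measure, to baseline and 6 months.

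The cost is a few more items for each woman in a booklet she already receives, plus wording changes. No extra visit, examination or staff time at sites is needed.

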## Outcome measures

The primary outcome, the Pelvic Organ Prolapse Symptom Score (POP-SS), will be assessed at baseline, 6 months and 12 months via a self-completed questionnaire. The POP-SS is a validated tool that includes seven items relating to the frequency of prolapse symptoms over the previous four weeks. Each item is scored from 0 (never) to 4 (all of the time) [23]. This questionnaire booklet will also measure secondary outcomes, assessing quality of life with the use of the EQ-5D-5L [24]; urinary incontinence with the ICIQ-UI short-form [25]; and service related outcomes including the need for further treatment. Six and 12 month questionnaires will also address the women’s adherence to the advice they have been given throughout the intervention (i.e. avoiding heavy lifting, changes to diet, weight loss) and also detail any further medical interventions that have been or are expected to be completed.

### POP-Q

Prolapse severity will be assessed as a secondary outcome with the use of the Pelvic Organ Prolapse Quantification system (POP-Q) [26]; a standardised and internationally recognised quantification system for prolapse. It is an objective, site-specific system for describing, quantifying and staging pelvic support in women. POP-Q will be performed for each woman in the outcomes study either by a consultant gynaecologist or a specialist women’s health physiotherapist trained to perform this assessment.

## Data analysis

### A) Realist Evaluation

Data from each round will be transcribed verbatim, organised using the data management software NVivo version 11, and analysed using a thematic analysis approach (Ritchie and Spencer [27]). Following familiarisation with the data by a minimum of two researchers, a thematic framework will be developed and agreed using data from a subsample of interview transcripts and the core concepts of the realist approach – contexts, mechanisms and outcomes. This framework will then be applied across the dataset through indexing of data segments. Indexing will be conducted by two researchers who will cross check a 10% sample of transcripts. Data will then be tabulated and conceptual maps used to make links between themes.

Data in each round will be summarised and synthesised across three sites to articulate the context (C) and mechanisms (M) of action and relate these to observed (quantitative and qualitative) outcomes (O) – leading to the development of CMO configurations. Round 1 and 2 data will be used to generate hypotheses about what potential mechanisms could or would be generated by the implementation, in what contexts, to achieve what outcomes. Round 3 data will be used to test these conjectured CMO configurations to understand what mechanisms were actually triggered in practice and how they were enabled or constricted by certain contexts. Finally, the hypothesised and observed CMOs will be used to test if they explain the complex patterning of outcomes of the PFMT implementation (qualitative and quantitative) gathered in round 4 and the outcomes study.

### B) Outcomes data

Descriptive statistics will be tabulated for all outcomes at each time point, showing means and SDs for POP − SS and EQ − 5D-5 L, proportions for POP − Q, the need for further treatment, and frequencies for the number of NHS contacts. Differences (and correlations where appropriate) between baseline and 6 − months and between baseline and 12 − months will be calculated. We will initially examine the differences before and after intervention using paired t-tests and chi-square tests. We will fit appropriate generalised linear models on the difference between outcomes before and after intervention, adjusting for baseline measurements and potential confounders (e.g. demographic factors, study site). If possible, we will also explore the effect of different levels of adherence to PFMT using structural mean models [28]. Complete case analyses will be performed throughout, with missing data being addressed in secondary analyses using multiple imputation methods.

POP − SS and EQ − 5D 5L will be treated as continuous data, POP − Q as ordinal, NHS contacts as count data and the need for further treatment (e.g. surgery or pessary) as binary data. In order to facilitate the understanding of prolapse related outcomes, individual items of the POP − SS will also be analysed separately and an additional dichotomous POP − Q measure (above/below the hymen) will be included in the analysis.

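### Chi-square tests are named for before/after comparisons in the same women: a paired categorical test should be named, and differences should not be the model response for ordinal, binary and count outcomes

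*Protocol article*

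**What the plan says.** The protocol article, Data analysis, B) Outcomes data, sets out two steps. The first is testing: "We will initially examine the differences before and after intervention using paired t-tests and chi-square tests". The second is modelling: "We will fit appropriate generalised linear models on the difference between outcomes before and after intervention, adjusting for baseline measurements and potential confounders". The next paragraph assigns data types. POP-SS and EQ-5D-5L are continuous and POP-Q is ordinal; for the rest it has "NHS contacts as count data and the need for further treatment (e.g. surgery or pessary) as binary data". It adds that "an additional dichotomous POP − Q measure (above/below the hymen) will be included in the analysis".

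The data are matched. The outcomes study is a single cohort measured before and after treatment, and Data collection, B) Outcomes study says "clinicians will collect POP-Q data at baseline and 6 months during specified appointments". No McNemar, marginal homogeneity or signed-rank test appears anywhere in the article.

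For service use, Data collection, C) Economic Evaluation describes questionnaires "administered at each of the follow up time periods".

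**The concern.** The word paired is attached to the t-tests and not to the chi-square tests. An analyst following the sentence literally would compare the POP-Q distribution before and after with a Pearson chi-square, which assumes that the two sets of observations are independent. They come from the same women, and prolapse severity in one woman at two times is likely to be positively correlated. The test then overstates the variance of the change, so its p-values are too large and real change can be missed. It also ignores the ordering that the plan itself gives to POP-Q stage.

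POP-Q is the clinician-assessed measure in an uncontrolled study whose other patient outcomes are self-reported, so a blunted test on it matters even though it is secondary.

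The modelling step does not clearly repair this. As worded, the response is the before/after difference for all outcomes, including those that the next paragraph calls ordinal, count and binary.

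**Working it through.** **Inputs from the protocol article.** 120 paired observations and two-sided alpha 0.05 (Sample size); POP-Q at baseline and 6 months in the same women (Data collection, B). The article gives no rate, correlation or power for any categorical outcome, so there is no figure of its own to reproduce on this point.

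**Assumed inputs.** 50% of women beyond the hymen before and 40% after; within-woman correlation phi of 0.3, 0.5 and 0.7.

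**Step 1: cell probabilities.** p11 = p0·p1 + phi·√[p0(1−p0)p1(1−p1)]. At phi 0.5 this is 0.20 + 0.5 × √(0.25 × 0.24) = 0.20 + 0.5 × 0.2449 = 0.3225. The discordant probabilities are 0.50 − 0.3225 = 0.1775 and 0.40 − 0.3225 = 0.0775, or 21.3 and 9.3 women of 120.

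**Step 2: the two statistics on the same expected table.**
- Pearson, time by category: 0.10² / (0.45 × 0.55 × 2/120) = 0.01 / 0.004125 = 2.42, p = 0.12. Phi does not enter, so the answer is the same whatever the correlation.
- McNemar: (21.3 − 9.3)² / (21.3 + 9.3) = 144 / 30.6 = 4.70, p = 0.03.

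**Step 3: true size of the Pearson test.** With equal margins p, the variance of the paired difference in proportions is 2p(1−p)(1−phi)/n, but Pearson uses 2p(1−p)/n. Its size is therefore P(|Z| > 1.96/√(1−phi)), which is 1.9%, 0.56% and 0.035% at phi 0.3, 0.5 and 0.7. Simulation at n = 120 and a 50% margin gives about 1.7%, 0.5% and 0.03%. McNemar stays between 4.8% and 5.4% over the settings tried.

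**Step 4: power by simulation, 50% to 40%, n = 120.**

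| phi | Pearson | McNemar, asymptotic | McNemar, exact |
|---|---|---|---|
| 0.3 | 31% | 46% | 40% |
| 0.5 | 27% | 60% | 52% |
| 0.7 | 22% | 83% | 77% |

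At phi 0, Pearson and asymptotic McNemar are nearly equal (33% and 34%), so the gap comes from the correlation.

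**Step 5: sensitivity.** With 90 complete pairs, Pearson has 22%, 18% and 12%, against 37%, 49% and 70% for asymptotic McNemar. For a larger fall, 50% to 35% at n = 120, Pearson has 68%, 71% and 76%, against 80%, 93% and over 99%. The direction does not change; the size of the loss depends on the assumed change and correlation.

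**Step 6: the model response.**
- Continuous outcomes: in a linear model adjusted for baseline, regressing the difference or the follow-up value gives the same coefficients for the other covariates. Only the baseline coefficient shifts, by 1. There is no problem here.
- Hymen dichotomy: the difference takes the values −1, 0 and 1, so a logistic model does not fit it.
- NHS contacts: a difference of counts can be negative, outside the range of a Poisson or negative binomial model.
- POP-Q stage: a difference of stages treats the steps as equally spaced and is no longer the ordinal variable that the plan describes.

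**Step 7: is there a baseline for service use?** The economic data-collection section mentions collection at follow-up only. Outcome measures places the need for further treatment in the questionnaire booklet, which is also used at baseline. The analysis section plans to tabulate every outcome, including further treatment and NHS contacts, at each time point. These three places do not settle the matter.

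**The case against.** The article never says Pearson. McNemar's test is itself a chi-square-type test, and the word paired could be read as governing both nouns. The step is described as initial, the outcomes are secondary, and a condensed article may leave the exact test to an analysis plan. This stands in part: the error is conditional on the ordinary reading. But the sentence does name a test, the usual meaning of that name is the unpaired one, and nothing else in the article points to a paired version.

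On the models, the word appropriate leaves the family and link open. It does not free the response, which is stated as the difference.

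Several stronger readings are tempting and are not supported:
- A reader might infer that POP-Q is certain to be analysed with an invalid test. The wording allows a valid one.
- A reader might imagine the chi-square run on the before-by-after cross-table, where it would test association and reject even with no change. The article speaks of examining differences, and nothing in it points to that use.
- A reader might call the difference undefined for binary and count outcomes. It can be formed wherever both values exist; it is ill-suited to logistic and count models.
- A reader might conclude that NHS contacts and further treatment have no baseline value. The sections conflict, so this is not established.

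**Conclusion.** The point holds as a moderate one. The protocol article names chi-square tests for matched before/after data and names no paired categorical test. Run as an ordinary Pearson test at n = 120 under the assumed 50% to 40% change, the loss against asymptotic McNemar is 15, 33 and 61 percentage points of power at phi 0.3, 0.5 and 0.7 (46 − 31, 60 − 27, 83 − 22). Against exact McNemar it is 9, 25 and 55 points (40 − 31, 52 − 27, 77 − 22). The direction of the error needs only a positive within-woman correlation. Its size rests on margins and correlations that the article does not give, so it cannot be said how often a real change would be missed in this study.

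The modelling sentence is unsuitable as worded for ordinal, binary and count outcomes, and the baseline status of the service-use outcomes is unresolved. The primary POP-SS comparison by paired t-test is unaffected, which is why this is not a must-fix item.

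**What to change.** 1. Replace the chi-square tests with named paired methods: McNemar's test, with a confidence interval for the paired difference in proportions, for the above/below-hymen dichotomy; and a Wilcoxon signed-rank or marginal homogeneity test for POP-Q stage. State whether McNemar is exact or asymptotic, since power differs by 6 to 8 points in the example.
2. In the regression sentence, keep the difference as response for continuous outcomes only. For the others, model the follow-up value with a matching family, adjusted for baseline where one exists: ordinal logistic for POP-Q stage, logistic for the hymen dichotomy and further treatment, negative binomial for NHS contacts.
3. Reconcile the economic data-collection section, Outcome measures and the outcomes analysis section on whether NHS contacts and need for further treatment are recorded at baseline. If they are not, analyse them as follow-up-only outcomes.

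The cost is a few sentences of wording, with no change to the sample size. Items 1 and 2 need no new data, and item 3 needs none if the outcomes are treated as follow-up only.

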### B) Outcomes study

Outcomes data will be collected before and after women receive the PFMT intervention in each location/model of service delivery to establish whether the improvements observed in the POPPY trial are also observed under different models of delivery and in non-trial real world NHS settings (see Table 2).

**Table 2 Tab2:** Outcomes Study site descriptions

Site	Urban/rural	POPPY experience	Current dominant model
1	Urban	POPPY recruiting centre	Primary and secondary care provision of specialist physiotherapy referred by primary care and acute services with a mix of 1:1 and group provision available. Women not routinely sent to physiotherapy as first line treatment. Several POPPY physiotherapists providing current input to women with POP
2	Urban	Large involvement in medically driven trials but no focus on physiotherapy based trials	Currently has some specialist physiotherapy involvement but greater specialist nurse-led service for women
		No POPPY involvement	
3	Rural	No POPPY involvement and limited other trial involvement	Current interest in re-design and expanding to junior grade physiotherapists and other nursing staff (as practitioners with special interest)
4	Urban	No POPPY involvement	Currently has some specialist physiotherapy involvement, looking to increase capacity for PFMT provision with other staff groups
5	Urban	No POPPY involvement	Currently has some specialist physiotherapy involvement, looking to increase capacity for PFMT provision with other staff groups

*PFMT* Pelvic Floor Muscle Training, *POP* Pelvic Organ Prolapse, *POPPY* Pelvic Organ Prolapse PhysiotherapY trial

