### Sample size

We have assumed that the minimum clinically important difference in the POP − SS is 2 [16] and that the standard deviation of the differences in POP − SS between baseline and one year will be 5.5 (as observed in POPPY). A sample size of 120 paired observations (with 2-sided alpha = 0.05) will therefore provide 80% power to detect important differences in POP − SS between baseline and one year.

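### The lead 12-month POP-SS analysis is complete case, so it leaves out the 6-month scores of women who do not reply at 12 months and is biased if their reply depends on those scores

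*Protocol article*

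**What the plan says.** The Data analysis section (B, Outcomes data) sets the order of the analyses: "Complete case analyses will be performed throughout, with missing data being addressed in secondary analyses using multiple imputation methods". In the same paragraph, changes from baseline to 6 months and from baseline to 12 months are calculated as two separate differences. The first step is "We will initially examine the differences before and after intervention using paired t-tests and chi-square tests". Generalised linear models for the difference follow, "adjusting for baseline measurements and potential confounders (e.g. demographic factors, study site"). The 6-month score is not named as a covariate for the 12-month difference.

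On data collection, the Outcome measures section says that POP-SS "will be assessed at baseline, 6 months and 12 months via a self-completed questionnaire". The Data collection section (B, Outcomes study) says that the questionnaire measures "will be collected by post at each time point".

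The design is uncontrolled: "Outcomes data will be collected before and after women receive the PFMT intervention in each location/model of service delivery". The Sample size section bases the study on the change from baseline to one year. It assumes that "the minimum clinically important difference in the POP − SS is 2" and that the standard deviation of the differences "between baseline and one year will be 5.5 (as observed in POPPY").

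**The concern.** Some postal non-response at one year is foreseeable, and some of the women concerned will have returned the 6-month questionnaire. Their 6-month scores carry information about where they would have stood at 12 months. Neither the paired t-test nor the baseline-adjusted model for the 12-month difference uses it.

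The complete-case mean change is valid if reply at 12 months is unrelated to outcome. The adjusted model is valid if reply depends only on the covariates in it. If reply depends on how the woman was doing at 6 months, both are biased, even though the data that would correct them have been collected. With no control arm, there is no comparison in which a similar response bias could cancel.

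At stake is the size of the 12-month improvement, which the study uses to judge whether the benefit seen in the earlier randomised trial is also seen in routine services. Change in POP-SS is also the effect measure in the economic evaluation. That evaluation compares delivery models, so there the bias matters only if response patterns differ between models.

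**Working it through.** **Is the harm loss of power?** From the Sample size section: difference 2, SD of differences 5.5, two-sided alpha 0.05. For 80% power, n = (5.5 × (1.960 + 0.842) / 2)² = 59.4, so 60 pairs. With 120 pairs, power = Φ(2√120/5.5 − 1.960) = Φ(2.02) = 97.8%. The stated 80% is not reproduced from these paired inputs, which is a separate point. What matters here is that the same formula gives about 95% power with 20% missing (96 pairs) and 92% with 30% missing (84 pairs); the noncentral t gives 94% and 91%. The harm, if any, is bias.

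**Assumptions for the bias.** The article gives no response rate and no correlations between visits, so these are assumed:
- SD of POP-SS 5.5 at each visit.
- Correlations 0.5 (baseline and 6 months), 0.5 (baseline and 12 months) and 0.7 (6 and 12 months). The SD of the baseline-to-12-month difference is then 5.5 × √(2 × (1 − 0.5)) = 5.5, as in the Sample size section.
- True change −2.0 (negative is improvement).
- Logistic loss at 12 months, with slope 0, 0.15 or 0.25 per point of 6-month POP-SS.

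**Simulation, 500 studies of 120 women (loss about 22-26% where it depends on the score).**

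| Slope | Complete-case mean change (SD) | Likelihood model using 6-month score (SD) |
|---|---|---|
| 0 | −2.02 (0.538) | −2.01 (0.518) |
| 0.15 | −2.21 (0.567) | −2.03 (0.541) |
| 0.25 | −2.33 (0.611) | −2.01 (0.580) |

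The SD ratios are 0.96, 0.95 and 0.95, so the likelihood model also has a 4-5% smaller standard error.

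**Large-sample check, same correlations and slopes, loss about 24-28%.**
- Complete-case paired change: −2.20 to −2.32.
- Complete-case model adjusted for baseline, evaluated at the baseline mean of all women: −2.46 to −2.76.
- Imputation of the 12-month score using the 6-month score: about −2.0.
- Dependence reversed, so that improved women stop replying: −1.81 for the complete-case paired change.

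**Check by hand.** When reply depends only on the 6-month score, the bias in the paired change is (0.7 − 0.5) × S = 0.2 × S. S is the 6-month mean of the 12-month responders minus that of all women. A bias of −0.20 to −0.32 therefore corresponds to S of −1.0 to −1.6 points.

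The same formula shows why baseline adjustment does not help. Responders also have a lower baseline, by about 0.5 × S, and in the paired change this cancels part of the bias. Adjusting to the baseline mean of all women, with a slope of change on baseline of about −0.5, removes that cancellation. For S = −1.0 the bias is −0.20 − (0.5 × 0.5) = −0.45, close to the simulated −0.46.

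**Sensitivity to harsher assumptions.** Here loss depends on whether the woman improved by at least 2 points: 10-20% loss if she did and 30-50% if not (20-30% overall), with a correlation of 0.3 to 0.7 between the 6- and 12-month changes.
- If loss depends on the 6-month change, complete case gives −2.16 to −2.88, a bias of 0.16 to 0.88 points. Using the 6-month data returns about −2.0.
- If loss depends on the unseen 12-month change, complete case gives −2.54 to −3.26, and imputation from the 6-month data −2.28 to −3.14. Bias is reduced, not removed.

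**The case against.** The sentence that puts complete case first also plans multiple imputation. If the imputation model includes 6-month POP-SS, it rests on the same missing-at-random assumption as a mixed model and would reveal the problem. The article does not list the imputation variables, but that is commonly left to an analysis plan. This stands: missing data are not ignored, and what is left is the order of two planned analyses. No analysis is labelled primary either. That complete case leads is inferred from imputation being called secondary, which is a fair inference.

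A reader might infer that these women are lost to the study. The text does not support that: the two differences are separate, and on the natural reading the women stay in the 6-month comparison.

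A reader might also infer that the benefit of PFMT will be overstated. Nothing in the article shows that non-improvers stop replying. With no dependence on the 6-month score there is no bias, and with the opposite dependence benefit is understated.

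The size is modest too. In the first simulation the bias is 0.21/0.567 = 0.37 to 0.33/0.611 = 0.54 of a standard error. The larger figures come from harsher assumed non-response.

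These points limit the weight of the concern but do not remove it. The article itself fixes the order, and the leading analysis needs the stronger assumption about non-response when data to relax it are already planned.

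**Conclusion.** The point holds for the baseline-to-12-month contrast, as a cheap improvement rather than a serious defect. Complete case leads, women with a 6-month but no 12-month score drop out of that contrast, and baseline adjustment does not correct for reply that depends on the 6-month score.

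Under the first set of assumptions the bias in the paired change is about 0.2-0.3 points, or 10-15% of the 2-point minimum important difference. Its size and direction rest wholly on assumed response patterns and correlations and cannot be derived from the article. Power is not at issue.

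It would go too far to call the alternative unbiased without qualification: it removes only the bias that arises under missing at random.

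**What to change.** Make the lead 12-month analysis one that uses 6-month POP-SS. Either of these will do:
- a likelihood-based repeated-measures model of the 0, 6 and 12 month scores, including every woman with a baseline score, with the 12-month-minus-baseline contrast leading; or
- the multiple imputation already planned, with 6-month POP-SS stated to be in the imputation model.

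Report complete case as a sensitivity analysis. Add a sensitivity analysis for reply that depends on the unseen 12-month score, for example by shifting the imputed values over a stated range.

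The cost is a change of wording in the analysis section and slightly more analysis work, with no new data. If reply proves unrelated to the 6-month score, nothing is lost: both approaches gave about −2.0 in that case. Clustering of women by clinician is a separate question and not part of this change.
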